## **9.4 Comparator Arm: Wait As Usual (WAU)**

No alternative evidence-based intervention is currently recommended, available, or implemented in the United Kingdom during the post-referral waiting period for patients waiting for a child health services assessment. WAU, therefore, is the most appropriate comparator. Those randomized to WAU will receive STEPS after they have completed the 12-month follow-up. In the sites across our three centres, we do not expect any patients to receive their clinical assessment and initiate treatment within the first three months of randomisation (T2) or few - if any - patients to engage in self-initiated treatment during this period. Parents will not be stopped from initiating their own access to services over the 12 months of the trial. All treatments received will be carefully recorded throughout the trial through the Child and Adolescent Service Use Schedule (CA-SUS; Barrett et al., 2012) and the Assessment & Diagnosis form (see Appendix 1).

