## 21. Harms

### 21.1 *Specification, Timing and Recording of Safety Parameters*

Please see section 21.2 below for adverse event definitions and reporting parameters. The risk of participants experiencing any adverse events during this trial as a result of using STEPS is very low. Adverse events concerning parental or child physical and mental health will be monitored throughout the trial. Any physical or mental health difficulties spontaneously disclosed by a parent in their communication with researchers will be entered into the Red Pill database using the OPTIMA adverse events form created specifically for the study (see Appendix 4). Moreover, at each timepoint, participants will be asked to complete a formal questionnaire on adverse events (Medical and psychological events and difficulties questionnaire) that happened to them and their child. This information will be collected online using ePRO. The forms will be reviewed regularly, and all adverse events will be recorded on the OPTIMA adverse events form in the Red Pill database. All participants that experience a serious adverse event will be followed-up by the researchers, who have completed Level 2 safeguarding training, until the event is resolved. Where necessary, the participant's clinical service which accepted the referral will be informed about the event.

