### 21.2 *Procedures for Recording and Reporting Adverse Events*

#### 21.2.1 Definitions of adverse events.

**Adverse Event (AE):** Any untoward medical occurrence in a subject to whom a therapy has been administered including occurrences which are not necessarily caused by or related to that therapy.

**Adverse Reaction (AR):** Any untoward and unintended response in a subject to a therapy which is related to any duration of therapy administered to that subject.

**Unexpected Adverse Reaction (UAR):** An adverse reaction the nature and severity of which is not consistent with the information known about the therapy in question in the view of the investigator

**Suspected Unexpected Serious Adverse Reactions (SUSAR):** Any serious adverse events that is deemed to be related to the trial intervention and unexpected (not listed in the protocol as an expected side effect of the intervention).

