#### 21.2.2 Adverse events reporting parameters

**An SAE occurring to a research participant should be reported to the main REC, where in the opinion of the Chief Investigator (CI) the event was:**

- Related – that is, it resulted from administration of any of the research procedures, and
- Unexpected – that is, the type of event is not listed in the protocol as an expected occurrence.

All SAEs, SARs and SUSARs (excepting those specified in this protocol as not requiring reporting) should be reported immediately to the Chief Investigator and to the Sponsor.

Reports of Serious Adverse Events (SAEs) that are **related** to the study (i.e., they resulted from administration of any of the research procedures) and **unexpected** (i.e., not listed in the protocol as an expected occurrence) should be submitted to the REC using the [Non-CTIMP safety report to REC form](#).

These should be sent within 15 days of the Chief Investigator becoming aware of the event. Reports of SAEs in double-blind trials should be unblinded. There is no requirement for annual safety reports in addition to the information provided through the annual [progress report](#). More detailed description of adverse events reporting parameters is included in Table 3.

Table 3. Adverse events reporting parameters.

|                                                                        | Who                | When                                                                                                                           | How                                                                                                                                                                                                                        | To Whom                                                                                                             |
|------------------------------------------------------------------------|--------------------|--------------------------------------------------------------------------------------------------------------------------------|----------------------------------------------------------------------------------------------------------------------------------------------------------------------------------------------------------------------------|---------------------------------------------------------------------------------------------------------------------|

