| Summary of final Report                                         | Chief Investigator | Within one year of conclusion of the Research                                                                                  | No Standard Format
However, the following Information should be included:
Where the study has met its objectives, the main findings and arrangements for publication or dissemination including feedback to subjects | Main REC with a copy to be sent to the sponsor                                                                      |

All completed adverse event questionnaires will be reviewed by the research team to identify any Suspected Unexpected Serious Adverse Reactions (SUSAR). If an event meets the definition of a SUSAR (see box below) then the member of staff to whom the event was disclosed must inform Chief Investigator within 24 hours of becoming aware of the serious adverse event and provide all necessary information. Each case will be assessed by the Chief Investigator and team clinical expert for seriousness, expectedness and relatedness to the study. The CI will then take appropriate action, which may include halting the study and informing the Sponsor of such action. If the event is deemed serious, unexpected and related to the study intervention they shall inform the REC using the reporting form found on the HRA web page within 15 days of knowledge of the event, and include the co-Sponsors (King's College London and The South London and Maudsley NHS Foundation Trust) in all communications. They shall, within a further eight days send any follow-up information and reports to the REC and make any amendments as required to the study protocol and inform the REC as required.

All SUSARs will be recorded and closely monitored by the research team until resolution, stabilisation, or until it has been shown that the study intervention is not the cause.

The electronic version of this document is the latest version. It is responsibility of the individual to ensure that any paper material is the current version. Printed material is uncontrolled documentation.

Any participant who experiences a SUSAR may be withdrawn from the study at the discretion of the CI and the Sponsor. Every withdrawal will be examined by the DMC. The DMC will be made aware of all serious adverse reactions/SUSARs at their regular meetings.

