### **25.4 Withdrawal of participants**

We do not expect using STEPS to lead to harm that would suggest the intervention needs to be discontinued. However, parents will be able to withdraw from the trial at any point for any reason. Through the information sheet, parents will be informed that they can withdraw from the study either by informing the team that they wish to opt out of taking part in follow-ups or by ignoring the reminders to complete the follow-up surveys. They can also stop using STEPS and delete the app from their phone at any time.

If a participant actively informs the research team that they would like to withdraw from the study, it will initially be clarified which aspects of the study they wish to withdraw (i.e., intervention, data collection or data collection from records) from and they will then be sent a 'confirmation of withdrawal' email and will be entered in the Red Pill database as withdrawn from the study. Copy of the email confirming withdrawal will be retained in the trial master file. Information about withdrawal will be shared with the participant's local clinical team. Participants will be made aware in the participant information sheets that any non-identifiable data collected up to the point of their withdrawal may still be used in the analyses. After withdrawal has been confirmed, participants will not be requested to complete any further measures but will be asked by the research team to provide voluntary feedback regarding the reason for their withdrawal. If feedback is provided, this will be recorded in the database. Once a participant has withdrawn from the study it will not be possible to re-enter the study or resume using the app. Withdrawn participants will not be replaced into the study.

Participants will not be withdrawn from the study due to poor engagement with the app. If a participant does not continue using STEPS, we would still invite them to complete outcome measures unless they explicitly state they wish to withdraw. In this case participants will be informed it is still key to the success of the study to collect outcome measures, even if they do not want to use the app.

Failure to complete outcome measures at one follow-up time point will not imply withdrawal from the study, and the participants will still be invited to complete measures at the next follow-up time point, unless they explicitly state otherwise.

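### The rule allowing withdrawal from the study after a SUSAR is not limited to the intervention, so it can end outcome and safety data collection, essentially only in the STEPS arm

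*Protocol*

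**What the plan says.** The withdrawal rule is in section 21.2.2: "Any participant who experiences a SUSAR may be withdrawn from the study at the discretion of the CI and the Sponsor". It does not require a request from the parent and does not limit the withdrawal to the app. The next sentence has the DMC examine every withdrawal.

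Section 21.2.1 defines a SUSAR as "Any serious adverse events that is deemed to be related to the trial intervention and unexpected". Section 9.4 adds: "Those randomized to WAU will receive STEPS after they have completed the 12-month follow-up".

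Two passages require follow-up of the event. Section 21.2.2 says "All SUSARs will be recorded and closely monitored by the research team until resolution, stabilisation", or until STEPS is shown not to be the cause. Section 21.1 says "All participants that experience a serious adverse event will be followed-up by the researchers", until the event has resolved.

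Section 25.4 sets out what withdrawal means. When a parent asks to withdraw, the team first clarifies whether this concerns the intervention, data collection or data from records. Then: "After withdrawal has been confirmed, participants will not be requested to complete any further measures". Re-entry is not possible, but "any non-identifiable data collected up to the point of their withdrawal may still be used in the analyses". The same section says that families who only stop using STEPS are still invited to give outcomes. Section 19.1 commits the main analysis to ITT as far as possible.

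**The concern.** The protocol distinguishes leaving the intervention from leaving data collection, but the SUSAR sentence does not use the distinction. A family that drops the app for lack of interest keeps giving data. A family whose serious event is attributed to the app may be taken out of the study by a decision that is not its own.

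Two things are at stake. The first is loss of follow-up that is triggered by attributed harm and depends on arm, which sits badly with the ITT aim. The second is safety information: MAPED is the safety measure at every timepoint (section 10.3.9, Table 2), and scheduled capture of later events in an affected family would stop. The second is the stronger ground, because it does not depend on how these children score on the primary outcome.

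**Working it through.** **Which arm the rule reaches.** The SUSAR definition requires a relation to the trial intervention, and WAU families have no access to STEPS until their 12-month follow-up is complete. During follow-up, an equally serious event in a WAU family would therefore not meet the definition. The wording is not uniform, however. For reporting serious adverse events to the REC, section 21.2.2 counts an event as related if "it resulted from administration of any of the research procedures", and it has each case assessed for its relation to the study. Either phrase could cover a WAU family. The same section then returns to the study intervention as the trigger for reporting and as the end point for monitoring. "Essentially" the STEPS arm is thus a fair reading; "only" is not fully secured.

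**What withdrawal would stop.** The only consequences of withdrawal in the protocol are those in 25.4: no further measures and no re-entry. The sentence on measures follows text about a parent who asks to leave, so applying it to a decision by the CI and Sponsor is an inference. The protocol states no other consequence.

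**When data would be lost.** SUSARs are identified by reviewing completed adverse event questionnaires (21.2.2) or from spontaneous disclosure (21.1). After randomisation MAPED is first due at T2, the same assessment as the primary SNAP-IV ODD score (Table 2). A SUSAR found that way would usually leave the T2 ODD score in hand, and data given before withdrawal may be used. The loss would then fall on T3 to T5. Only an event disclosed before T2 could cost a primary score.

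**Size on the primary outcome.** Inputs from section 13: d = 0.4 SD, two-sided alpha 0.05, 90% power, 25% drop-out, 176 per arm.

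- Reproduction: 2 × ((1.960 + 1.282)/0.4)² = 131.3, so 132 analysed per arm (power 90.1%). Then 132/0.75 = 176 per arm, 352 in total. The plan's figure reproduces.
- Illustration: if k of 132 STEPS families are lost before T2, and their ODD would have been D SD worse than the rest of the arm, the STEPS mean shifts in its own favour by k × D/132.
- The protocol gives neither k nor D; both are assumptions. It expects no serious harms from the intervention (section 16).

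| k | D = 1 | D = 1.5 | D = 3 |
|---|---|---|---|
| 1 | 0.008 SD (2% of 0.4) | 0.011 SD (3%) | 0.023 SD (6%) |
| 3 | 0.023 SD (6%) | 0.034 SD (9%) | 0.068 SD (17%) |
| 5 | 0.038 SD (9%) | 0.057 SD (14%) | 0.114 SD (28%) |

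For scale, the standard error of the difference with 132 per arm is √(2/132) = 0.123 SD, so the shift for one family at D = 1.5 is about 9% of a standard error (0.011/0.123). Power stays at 89.6% or more with up to five families lost.

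**The case against.** A reader might infer three stronger things, and the documents support none of them.

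- *That the rule removes the worst STEPS outcomes.* Withdrawal is optional, earlier data may be kept, and the DMC examines each case. A SUSAR must also be unexpected, while section 21.3 lists deterioration in child behaviour, including self-harm, as expected. The events most closely tied to a poor ODD score are therefore not SUSARs by type. An unexpected event could be medical or concern the parent, with no stated link to ODD. Neither the size nor the direction of a bias is established.
- *That the rule contradicts the duty to follow the event.* Monitoring of an event by research staff can continue after questionnaires stop. The protocol does not say how the two fit together, which is a gap and not a contradiction.
- *That a SUSAR can by definition occur only under STEPS.* The wider relatedness wording in 21.2.2 leaves some room for a WAU case.

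It can also be said that the larger entries in the table should carry no weight. That is right: several SUSARs before T2, each followed by withdrawal and each with a much worse ODD score, is a remote combination, and 21.2.2 lets the CI halt the study after a SUSAR.

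What remains is that the sentence, as written, allows the whole study to end for a family after harm attributed to STEPS, while 25.4 takes care to keep other families who leave the app. DMC examination is a safeguard, but the text does not say that it comes before a withdrawal or can reverse one.

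**Conclusion.** The point holds as a minor one. The SUSAR sentence in 21.2.2 is not reconciled with 21.1, with the follow-up duty in its own section, with 25.4, or with the ITT aim in 19.1. It permits harm-related loss of outcomes and of later safety data, essentially in one arm and mainly at T3 to T5.

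The likely effect on the primary estimate is very small: about 0.01 SD, or 3% of the target difference, for one family lost before T2 and assumed 1.5 SD worse. That figure rests on assumed values of k and D. The conclusion that measures stop rests on carrying 25.4 over to a decision by the CI and Sponsor. The sample size is unaffected.

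**What to change.** Reconcile 21.1, 21.2.2 and 25.4. State in 21.2.2 that a decision by the CI and Sponsor after a SUSAR does not by itself end data collection, and that scheduled outcome measures, MAPED and T5 record extraction continue to be offered in both arms unless the parent declines. Say how follow-up of the event proceeds in such a family, and use one relatedness wording for SUSARs throughout. Whether STEPS use continues after a SUSAR remains a clinical decision, and no rule on it is proposed here.

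The cost is a small wording amendment and a few more questionnaires offered to affected families, which the parent may decline.

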## **9.2 Frequency and duration of intervention**

Participants in the treatment arm will have access to STEPS for 3 months. STEPS is a self-guided intervention and the time needed to complete each module (step) will depend on the pace of the individual user. However, each of the eight modules are designed to take about 20 minutes if completed in one go. Completion of the two first modules: ‘Make a fresh start’ and ‘Look after yourself’ will constitute adherence to the intervention.

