### **20.2 Data Monitoring Committee**

The Data Monitoring Committee (DMC) is an independent body of experts that has been established to monitor the quality of trial data and the safety of participants. The DMC will have access to unblinded data if they wish. The DMC will be responsible for monitoring the overall conduct of the study, including recruitment, protocol compliance, accuracy and completeness of data collection. Based on this information, the DMC will make recommendations to the PSC, the Funder and the Sponsor on whether the study should continue or whether there are any ethical or safety reasons why the study should be modified or terminated. Any key changes to the study design and methodology will be reviewed by the DMC. The members of the DMC are completely independent of the trial and consist of an independent chair, statistician, and clinical

The electronic version of this document is the latest version. It is responsibility of the individual to ensure that any paper material is the current version. Printed material is uncontrolled documentation.

expert. The DMC will meet approximately every six months, shortly before a PSC meeting. One of the meetings will coincide with the end of the internal pilot, to determine whether the trial should continue. The DMC and the PSC will be given a charter to outline their tasks and responsibilities.

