### **21.4 Progression Criteria / Stopping Rules**

The study will include an internal pilot study (the first 9-months of recruitment). There are no formal statistical stopping rules; progression rules for the internal pilot are described in Table 4 below. The trial may be prematurely discontinued by the Sponsor or Chief Investigator based on new safety information or for other reasons given by the DMC or PSC regulatory authority or ethics committee concerned.

Another reason for stopping the trial prematurely would be poor recruitment and engagement with the STEPS intervention or attrition during the pilot phase, which does not improve despite efforts to engage clinical teams and parents of referred children. This will be reviewed after the 9-month internal pilot. If the

The electronic version of this document is the latest version. It is responsibility of the individual to ensure that any paper material is the current version. Printed material is uncontrolled documentation.

internal pilot targets for recruitment, engagement or attrition are not met (below), the trial may be terminated on consensus advice of the PSC, DMC and the study funder.

The objective of the internal pilot is to determine whether recruitment, engagement with the intervention and retention to the trial are sufficient to allow the trial to progress and provide a definitive answer on the effectiveness of the intervention. Progression rules regarding recruitment, treatment engagement and attrition during the internal pilot are specified in Table 4. Briefly, green means that the trial will continue, amber – the research team will review ways of improving with the PSC and the Patient and Public Involvement (PPI) Steering Group. The decision to continue or stop the trial will be made independently by the PSC taking advice from the DMC.

Table 4. OPTIMA RCT internal pilot progression rules.

| RECRUITMENT                                                                                                                                                                                                                                                                                                                                                                                   |

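### The protocol gives no expedited route to the DMC for serious adverse reactions or SUSARs; on its stated timetable the DMC could learn of one up to about six months later, twice the length of STEPS access.

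*Protocol*

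**What the plan says.** Section 20.2 gives the DMC responsibility for participant safety and for recommending whether the study should be changed or stopped on safety or ethical grounds. On timing it states "The DMC will meet approximately every six months, shortly before a PSC meeting". Section 21.2.2 then says how serious events reach it: "The DMC will be made aware of all serious adverse reactions/SUSARs at their regular meetings". No other timing for telling the DMC is given.

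Other recipients hear sooner. Under section 21.2.2, serious events and reactions go immediately to the Chief Investigator and Sponsor. The person who learns of a possible SUSAR "must inform Chief Investigator within 24 hours of becoming aware of the serious adverse event", and "The CI will then take appropriate action, which may include halting the study and informing the Sponsor of such action". Serious events that are both related and unexpected go to the REC within 15 days, and Table 3 has urgent safety measures telephoned to the REC at once.

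On exposure, section 9.2 says "Participants in the treatment arm will have access to STEPS for 3 months". On stopping, section 21.4 says "There are no formal statistical stopping rules; progression rules for the internal pilot are described in Table 4 below". Table 4 covers recruitment, engagement and attrition only, although the text of 21.4 also allows discontinuation on new safety information.

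**The concern.** A SUSAR is, by the definition in section 21.2.1, serious, unexpected and judged related to the intervention. It is the kind of event that would test the protocol's expectation that STEPS carries very little risk. Yet the one rule on telling the DMC ties the news to a roughly six-monthly calendar.

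This matters because of who can see what. Section 16 keeps the Chief Investigator and Principal Investigators blinded until the finalised statistical report. Before the statistical report is reviewed, only the junior statistician, the junior health economist and the DMC can see data by arm. Section 20.2 gives the DMC unblinded data on request. So among the bodies that advise or decide on continuation, only the DMC can set a new event against the accumulating data by arm. The Programme Steering Committee is no quicker, since section 20.1 has it meet about every six months too. At stake is how many more families start the app before that review can happen.

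**Working it through.** **Inputs.** Total 352, 176 per arm, d = 0.4, two-sided alpha 0.05, power 90%, drop-out 25% (section 13). Recruitment 24 months and overall duration 39 months (section 12). Allocation 1:1 (section 15). DMC interval about 6 months (section 20.2). STEPS access 3 months (section 9.2).

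**The plan's own figure.** n per arm = 2(1.960 + 1.282)² / 0.4² = 131.3, rounded up to 132. Inflated for drop-out, 132 / 0.75 = 176 per arm, or 352 in total. The stated sample size reproduces.

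**STEPS starts between two DMC meetings.** The protocol gives no such figure, so even accrual is assumed. Starts = (352 / recruitment months) × months waited × 1/2.

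| Enrolment period | Families per month | Randomised in 6 months | STEPS starts, full 6-month wait | STEPS starts, average 3-month wait |
|---|---|---|---|---|
| 24 months (section 12) | 352/24 = 14.67 | 88 | 44 | 22 |
| 27 months (39 − 12, assumed) | 352/27 = 13.04 | 78.2 | 39.1 | 19.6 |

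The full wait applies to an event that becomes known just after a meeting. An event at a random time waits 3 months on average. The ceiling of 44 is 44/176 = 25% of the STEPS arm. At half the planned recruitment rate the 24-month figures halve, to 22 and 11.

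**Against the 15-day clock.** At 14.67 / 2 = 7.33 STEPS starts per month, 15 days (15/30.4 of a month) covers about 3.6 starts.

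**Against the access period.** The interval is 6/3 = 2 times the access period. About 7.33 × 3 = 22 families are within their access period at any time in steady recruitment. With a full six-month wait, all of them would have finished before the DMC met, and a family could start and finish STEPS between two meetings.

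**The case against.** A reader might infer that no safety event ever prompts a DMC review. The protocol does not support that. Just before the sentence at issue, section 21.2.2 says "Any participant who experiences a SUSAR may be withdrawn from the study at the discretion of the CI and the Sponsor" and then "Every withdrawal will be examined by the DMC". This is a DMC review linked to safety. It is not a prompt route, because withdrawal is discretionary and the examination has no stated timing, but it rules out the absolute claim. Section 20.2 also promises the DMC a charter, which is not shown and could provide for unscheduled meetings or notice to the chair. What can be said is that the protocol states no expedited route, not that none exists.

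A reader might also infer that nothing happens for six months, or that 44 further starts are to be expected. Neither follows. The Chief Investigator, the Sponsor and the REC all hear earlier, the REC is independent, and section 21.4 lets the ethics committee's reasons stop the trial. The figure of 44 needs an event just after a meeting and no action by any of them.

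Finally, section 21.1 calls the risk very low and section 16 expects no serious harms, so it can be said that regular reporting is proportionate for an unguided parenting app. That bears on how often the route would be used. It also means that the change would cost almost nothing. The charter argument stands as a limit on the finding. If the charter already has such a route, section 21.2.2 should refer to it, because as written it points only to regular meetings.

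**Conclusion.** The point holds in limited form. On the protocol's text, the DMC could learn of a serious adverse reaction or SUSAR up to about six months after others do, which is longer than the 3-month access to STEPS. That corresponds to at most 44 further STEPS starts and about 22 on average (39 and 20 if enrolment takes 27 months). These figures assume even accrual, 1:1 allocation, no pause by the Chief Investigator, Sponsor or REC, and no faster route in the charter. How often a SUSAR would occur is not estimated.

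The protocol does not contradict itself on DMC timing. This is a worthwhile and inexpensive improvement to a stated rule, and no numerical stopping boundary is implied.

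A related inconsistency needs reconciling. Section 21.2.2 ends by saying that events listed as expected need not be reported, and refers to a section 20.3 that the protocol does not contain. Section 21.3 says that expected events meeting the criteria for a serious adverse reaction will be reported. Since the 15-day REC report is limited to events that are related and unexpected, it is unclear whether an expected but serious reaction reaches the REC at all.

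**What to change.** Amend the DMC sentence in section 21.2.2 to say that:

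- each SUSAR report is copied to the DMC chair when it goes to the REC;
- each other serious adverse reaction is notified to the chair on the same clock, within 15 days of the Chief Investigator becoming aware;
- the chair decides whether to convene the DMC before its next scheduled meeting;
- the cumulative list is still tabled at every regular meeting.

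Refer to this in section 21.4 and in the DMC charter. If the charter already has an equivalent provision, a cross-reference to it in section 21.2.2 is enough. Reconcile the end of section 21.2.2 with section 21.3 on expected events that meet the serious-reaction criteria, and correct the section number. The Sponsor and DMC can settle the exact interval.

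The cost is a short protocol amendment, one more addressee on the SUSAR report, a brief separate notice for serious reactions that do not otherwise go to the REC, and an occasional unscheduled DMC call. No new committee or data collection is needed.
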